### Safety and adverse events

2.12

Safety indicators will be recorded before and after 4 weeks of treatment including:

1.vital signs, such as body temperature, blood pressure, respiration, and heart rate;2.blood routine, urine routine;3.electrocardiogram;4.liver function (ALT, AST), renal function (BUN, Cr), etc.

Standard operating procedures for handling all adverse events will be monitored and reported, including occurrence time, severity, duration, effective measures, and results. Investigators will decide whether to suspend or withdraw the trial based on the severity of adverse events. In case of any serious adverse event, the researchers will report it to the principal investigator ([name]) and the Medical Ethics Committee within 24 h. Guang’anmen Hospital provided insurance for injuries caused by interventions during the trial period.

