### Inclusion criteria

2.6

1.Conforms to the diagnostic criteria of unstable angina pectoris, set out in the guidelines for the diagnosis and treatment of unstable angina pectoris and non-ST-segment elevation myocardial infarction published by the Chinese society of cardiovascular diseases. The diagnostic criteria of TCM syndromes are consistent with phlegm and blood stasis obstruction syndrome.2.Patients with coronary heart disease confirmed by coronary angiography (1 or more major coronary artery stenosis degree ≥ 50%).3.Aged 35 to 75 years.4.Voluntary participation in this clinical study and signed informed consent form. Subjects must take the medicine for 4 weeks, complete the scale and test before and after treatment. A fixed contact way to complete the follow-up work is also requisite.

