### Intervention

2.10

The loading test method will be used. Both groups will be treated with routine western medicine. The routine western medicine treatment is strictly in accordance with the “Guidelines for the Management of Unstable Angina Pectoris-Non-ST Segment Elevation Myocardial Infarction 2012ACCF/AHA.” The experimental group will be given GLDS, 6 g, three times a day. The control group will be given placebo granules, 6 g, three times a day. The placebo is mainly composed of starch, which ensures that the shape and odor of the placebo granules are the same as those of the GLDS. The course of treatment was set for 4 weeks, during which no other Chinese patent medicine or decoction was used to treat coronary heart disease.

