### Outcomes

2.11

Incomplete data will affect the judgment of efficacy and safety, so it can only be adopted when the data integrity is over than 80%, data that does not meet this requirement will be excluded. The data collected will be the following:

1.Clinical Symptom Rating Scale (supplementary file 1);2.Phlegm-Blood Stasis Syndrome Scale (supplementary file 2);3.Seattle Angina Questionnaire (supplementary file 3);4.Chinese medicine syndrome efficacy evaluation criteria in accordance with the Guidance of Clinical Research on New Chinese Medicine for Coronary Heart Disease Angina Pectoris issued by the Ministry of Health of the People's Republic of China in 2002.

The efficacy calculation is as follows: Curative effect index (n) = (pre-test integral-post-test integral)/pre-test integral × 100%. Effectiveness is defined as: significant effect: the clinical symptoms and signs were significantly improved, and the integral of TCM syndromes was reduced by more than 70%. Effective: The clinical symptoms and signs were improved, and the integral of TCM syndromes was reduced by more than 30%, <70%. Invalidity: Clinical symptoms and signs did not improve significantly, or even worsened, the TCM syndrome score decreased by less than 30%. Aggravation: clinical symptoms and signs were aggravated, and the integral of TCM syndromes decreased <0.

All the scales will be completed on the day of registration and after taking the medicine for 4 weeks. We will compare the index changes before and after taking the drug and perform data collation for statistical analysis in order to evaluate the effectiveness of GLDS in the treatment of unstable angina pectoris.

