### Data management and statistical analysis

2.13

The general data, safety indicators and therapeutic effect of angina pectoris are to be observed before and after treatment. SPSS 20.0 statistical software will be used for data analysis. The measurement data will be expressed as mean (+standard deviation). One-way analysis of variance will be used for comparison among multiple groups, and the homogeneity of variance test will be conducted using the Levene method. If the variance is homogeneous, LSD-T test will be used for pair comparison. If the variance is not uniform, the Tamhane method will be used for pair comparison. Non-normally distributed data will be represented by median and quartile, using rank sum test. *P* < .05 will be considered statistically significant.

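### Week-4 scales and safety tests are timed by medicine taken, and completing the course is an inclusion criterion, which favours a completers-only comparison

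*Protocol article*

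**What the plan says.** The protocol article has one baseline and one post-baseline measurement, and it words the second by treatment received.

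- Section 2.11 (Outcomes), on the scales: "All the scales will be completed on the day of registration and after taking the medicine for 4 weeks".
- Section 2.12 (Safety and adverse events), on vital signs, blood and urine tests, ECG, and liver and renal function: "Safety indicators will be recorded before and after 4 weeks of treatment including".
- Section 2.13 (Data management and statistical analysis): "The general data, safety indicators and therapeutic effect of angina pectoris are to be observed before and after treatment".
- Section 2.10 (Intervention) sets one fixed duration: "The course of treatment was set for 4 weeks".

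Two further rules bear on who is counted. Section 2.6 lists under inclusion criterion 4: "Subjects must take the medicine for 4 weeks, complete the scale and test before and after treatment". Section 2.11 says of incomplete data: "it can only be adopted when the data integrity is over than 80%, data that does not meet this requirement will be excluded".

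Adverse events have their own provision in section 2.12, which is not tied to week 4: "Standard operating procedures for handling all adverse events will be monitored and reported, including occurrence time, severity, duration, effective measures, and results".

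**The concern.** An inclusion criterion should be checkable before randomisation. Whether a patient takes four weeks of medicine and returns for the tests is known only afterwards and may depend on the treatment received. Placed among the eligibility conditions, it lets a site regard a randomised patient who stops as someone who should not have been in the trial.

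The visit wording points the same way. If the follow-up measurement is defined as coming after four weeks of medicine, a patient who stopped sooner has no point in the written schedule that clearly applies. The 80% rule can then remove whatever that patient did contribute.

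The randomised comparison is at stake. Patients who stop because of poor tolerance or lack of effect are not a random subset, and they need not be alike in the two arms. Safety is half of the objective in section 2.1, so this matters for the laboratory and ECG comparison as much as for the scales. An analysis plan can choose how to handle a missing value, but it cannot recover a measurement that was not taken.

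**Working it through.** The article gives no figure of its own for this point, so the check is mainly a reading of the passages together, followed by simple arithmetic on size.

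**1. What anchors each follow-up item**

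| Item | Section | Anchor |
|---|---|---|
| Scales | 2.11 | medicine taken for 4 weeks |
| Safety tests | 2.12 | 4 weeks of treatment |
| Safety indicators and effect, for analysis | 2.13 | before and after treatment |
| Eligibility | 2.6, criterion 4 | 4 weeks of medicine plus after-treatment tests |
| Drug count and compliance | 2.14 | 4 weeks, by calendar |

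Only the drug count is timed without reference to medicine taken. It also provides for returned drug, so incomplete intake is expected. No section fixes the scales or safety tests by time since randomisation.

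**2. How the 80% rule acts on a patient without the second measurement**

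The article does not say how data integrity is counted. Assume it is the share of scheduled measurements obtained for a patient. With two time points, a patient measured only at baseline has 1/2 = 50%, which is below 80%, and is excluded.

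**3. How many patients**

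Inputs from section 2.9: 30 per group, 60 in total, drop-out below 5%.

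- The drop-out step reproduces: 28/0.95 = 29.5, rounded up to 30 per group.
- 5% of 60 = 3, so strictly below 5% means at most 2 patients.
- One patient is 1/30 = 3.3% of an arm.
- If the limit is not met: an assumed 10% gives 6 of 60, and an assumed 15% gives 9 of 60. Neither rate is in the article.

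**4. What two patients can do to a response rate**

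Take the 86.2% effective rate from section 2.9 and assume that both early stoppers are in the GLDS arm, leaving 28 completers.

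- Responders among completers: 0.862 × 28 = 24.1, taken as 24. Completers' rate: 24/28 = 85.7%.
- All 30 randomised, neither early stopper a responder: 24/30 = 80.0%.
- All 30 randomised, both responders: 26/30 = 86.7%.

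The completers' figure could therefore be up to 5.7 percentage points too high or about 1 point too low. This bounds what two missing patients could do and does not predict what they will do.

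The article gives no expected rate of laboratory or ECG abnormality. For safety, no size is given beyond 3.3% of an arm per unmeasured patient.

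**The case against.** The strongest reply is that this is a condensed article describing a fixed four-week course. In that setting, wording such as after four weeks of treatment is ordinary shorthand for the week-4 visit. The calendar-timed drug count in section 2.14 supports that reading. Criterion 4 sits in the same item as voluntary participation and consent, and also asks for a fixed means of contact for follow-up, so it can be read as an undertaking the patient gives at entry. Any early-termination visit may be in the full protocol, which is not shown.

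Much of this stands. A reader might infer that patients who stop early have no follow-up at all. The documents do not support that: no section says so, and silence in a journal article does not establish it. A reader might also infer that reactions leading to discontinuation would go unseen. That is not supported either. Section 2.12 covers the time, severity, duration, management and result of all adverse events, and section 2.2 provides an independent data and safety monitoring committee. A raised laboratory value already known when a patient stops could be captured as an adverse event. Nor does any section say that a randomised patient who stops becomes ineligible.

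The reply does not remove the wording itself. Criterion 4 states a condition that arises after randomisation, and the treatment-based timing is the article's own text. Adverse-event recording does not fully replace scheduled testing, because a laboratory or ECG change without symptoms is found only if the test is done.

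**Conclusion.** The point holds as a fault of wording with a real consequence if it is followed literally. Sections 2.6, 2.11 and 2.12 together favour a completers-only comparison of the scales and of laboratory and ECG safety. They also allow a nominal week-4 reading, and the article does not say which is meant.

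The expected size is modest: at most 2 of 60 patients if the drop-out limit is kept, each 3.3% of an arm, with a possible overstatement of up to 5.7 percentage points in one arm's response rate in the extreme case shown. This assumes that early stoppers fall within the planned drop-out, that both are in one arm, and that data integrity is counted per patient. More patients could be affected if the limit is missed. The point does not rest on the absence of an early-termination visit, which the full protocol may contain.

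**What to change.** - In sections 2.11 and 2.12, state that the existing week-4 scales and safety tests are taken 4 weeks after randomisation in every randomised patient, whether or not the medicine is still being taken.
- In section 2.6, reword criterion 4 as willingness to take the medicine and attend the assessments, so that stopping treatment does not make a randomised patient ineligible.

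The change is to wording and adds no new test or visit to the schedule. The small downside is the effort of contacting and assessing the few patients who stop early, for which criterion 4 already requires a means of contact.

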### Data management and statistical analysis

2.13

The general data, safety indicators and therapeutic effect of angina pectoris are to be observed before and after treatment. SPSS 20.0 statistical software will be used for data analysis. The measurement data will be expressed as mean (+standard deviation). One-way analysis of variance will be used for comparison among multiple groups, and the homogeneity of variance test will be conducted using the Levene method. If the variance is homogeneous, LSD-T test will be used for pair comparison. If the variance is not uniform, the Tamhane method will be used for pair comparison. Non-normally distributed data will be represented by median and quartile, using rank sum test. *P* < .05 will be considered statistically significant.

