### Randomization and blinding

2.8

The randomized grouping method will be used by the clinical evaluation center of the Chinese Academy of Medical Sciences. Random grouping tables will be generated by SAS 6.12 statistical software. The sixty eligible participants will be assigned to either the GLDS group or placebo group in a ratio of 1:1. All drugs will be labeled by pharmaceutical companies according to the random grouping table. Double blindness will be guaranteed during the whole experiment. Random grouping numbers will be stored in opaque sealed envelopes until the end of the experiment or an emergency occurs.

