### Sample size estimation

2.9

According to the calculation formula of sample size, the total effective rate of GLDS is 86.2% in combination with previous clinical study information. Consequently, the test set *a* = 0.05, beta = 0.10, *f* (*a*, beta) = 10.5, using a unilateral test, the initial estimated sample number was 27.5, and the integer number was 28. According to the test funds and other related issues, the drop-out rate was limited to <5%. The number of cases in each group was set at 30, and the total number of cases in two groups at 60.

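### The stated analysis uses multi-group ANOVA wording for a two-arm trial and names no comparison of the total effective rate on which the trial was sized

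*Protocol article*

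**What the plan says.** - **Design (2.8 Randomization and blinding).** Sixty participants are "assigned to either the GLDS group or placebo group in a ratio of 1:1". There are two arms and no third group.
- **Sizing (2.9 Sample size estimation).** The calculation rests on a proportion: "the total effective rate of GLDS is 86.2% in combination with previous clinical study information". It continues with "the test set *a* = 0.05, beta = 0.10", a constant f of 10.5, and "using a unilateral test, the initial estimated sample number was 27.5, and the integer number was 28". The final size is 30 per group. No control-arm rate is given.
- **Outcomes (2.11).** Four measures are listed without ranking, and none is called primary. Four ordered response categories are defined from the percentage fall in the TCM syndrome score. The total effective rate is presumably the share of patients in the two favourable categories. Scales are completed at registration and after 4 weeks, and the text speaks of comparing changes from before to after treatment.
- **Analysis (2.13 Data management and statistical analysis).** Measurement data get mean and standard deviation. Then: "One-way analysis of variance will be used for comparison among multiple groups", with Levene's test for variances. "If the variance is homogeneous, LSD-T test will be used for pair comparison"; otherwise Tamhane is used. Non-normal data get median and quartiles with a rank sum test. The significance threshold is P < .05, with no sidedness stated. No test, estimate or interval is named for a rate or any other categorical outcome.

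**The concern.** Two things do not fit together.

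First, the number of patients is justified by a comparison of proportions, but the analysis section goes into some detail on methods for measurement data and stops there. An analyst who follows it as written never tests the outcome that justified 60 patients, so the 90% power is not attached to any analysis that will be run.

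Second, post-hoc pairwise tests have nothing to act on when there is one between-arm pair. Because both 2.11 and 2.13 use before/after language, a reader can also take the comparisons to be within each arm, or between arm-and-visit cells. Both arms receive routine western treatment (2.10), so a within-arm improvement would not show an effect of GLDS.

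**Working it through.** **1. The plan's sample size.** Inputs from 2.9: p1 = 0.862, alpha = 0.05, beta = 0.10, f = 10.5, n = 27.5 per group, rounded to 28. The control rate p2 is not stated, so 27.5 cannot be rebuilt. It can only be solved backwards.

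- Two-sided constant: (1.960 + 1.282)² = 10.51. One-sided constant: (1.645 + 1.282)² = 8.56. The stated 10.5 is therefore the two-sided value, although the text says the test is one-sided.
- Formula: n = f × [p1(1−p1) + p2(1−p2)] / (p1−p2)².
- With f = 10.5, n = 27.5 implies p2 ≈ 0.487. Check: 10.5 × (0.1190 + 0.2498) / 0.3752² = 3.872 / 0.1408 = 27.5.
- With f = 8.564, n = 27.5 implies p2 ≈ 0.523.
- Dropout: 28 / (1 − 0.05) = 29.5, rounded up to 30. This matches the document.

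The figure thus behaves like a two-proportion calculation with an unstated control rate of about 49% to 52%. The power in 2.9 is power for comparing two rates.

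**2. Does 2.13 contain that comparison?**

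| Procedure named in 2.13 | Data it is for | Compares the effective rate? |
|---|---|---|
| One-way ANOVA with Levene | measurement data | no |
| LSD-t | measurement data, equal variances | no |
| Tamhane | measurement data, unequal variances | no |
| Rank sum | non-normal data shown as median and quartiles | no |

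**3. What the multi-group text does with two arms.**

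- One-way ANOVA with two groups is the pooled t-test. In a simulated data set with 30 per arm, F = t² = 5.560 and P = 0.0218 for both.
- LSD on the single pair is the same t-test.
- Tamhane's per-comparison level is 1 − (1 − 0.05)^(1/k). With k = 1 this is 0.05, so no adjustment remains.

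The wording is redundant and does not inflate error.

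**4. Power if the missing test is added at 30 per arm.** Normal approximation: power = Φ{[(p1−p2)√n − z√(2p̄q̄)] / √(p1q1 + p2q2)}, where p̄ is the mean of p1 and p2, and each q is 1 − p. For p2 = 0.50, two-sided: (0.362 × 5.477 − 1.960 × 0.659) / 0.607 = 1.14, which gives 87%. The control rates below are assumptions.

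| Assumed control rate | Two-sided 0.05 | One-sided 0.05 |
|---|---|---|
| 47% | 92% | 96% |
| 50% | 87% | 93% |
| 55% | 77% | 86% |
| 60% | 63% | 75% |
| 70% | 33% | 45% |

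Sidedness alone moves power by 4 to 12 points, so it has to be settled when the test is written in.

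**5. The before/after wording.** If arm and visit were crossed, there would be 4 × 3 / 2 = 6 pairs. Only one of these, GLDS against placebo at week 4, is the randomised comparison of outcome. Two are within-arm changes, one is a baseline comparison, and two mix arm with visit.

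**The case against.** **The multi-group text is harmless boilerplate.** This largely stands. On the stated two-arm design it reduces to valid t-tests, and a between-arm comparison of change scores is itself valid under randomisation.

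**This is a condensed article.** The full protocol and the analysis plan are not shown, and a line on chi-square tests is the kind of detail an article may leave out. This limits the claim: nothing can be said about what an unseen plan contains. It does not remove the point, because 2.13 names specific procedures, and these do not match the article's own two-arm design or its own sizing endpoint.

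**The rank sum test could serve the ordered response categories.** It could, but the text ties it to non-normal data reported by median and quartiles. It would still not compare the effective rate.

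**A stronger reading to avoid.** A reader might infer four groups (arm by visit) and conclude that six unadjusted LSD tests give about a 20% chance of a false positive. The documents do not support this. No section describes four cells, and the talk of before/after changes fits one change value per patient just as well. Even on that assumed reading, simulation with 28 per cell and no true differences gives about 20% only with independent cells and no requirement of a significant overall F. The figure is about 14% with an assumed within-patient correlation of 0.5, and about 5% and 4% respectively once a significant F is required.

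A reader might also take the effective rate to be the declared primary outcome. The article sizes on it but designates no primary outcome.

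**Conclusion.** The point holds in a limited form and should be fixed.

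- **Main defect.** The stated 90% power is for a between-arm comparison of the total effective rate, and the stated analysis includes no such comparison. This follows from reading 2.9 against 2.13 and needs no outside assumption.
- **Secondary defect.** The multi-group and pairwise wording does not fit two arms, and the before/after language leaves open comparisons that are not the randomised one.
- **Size.** There is no error inflation on the two-arm reading. The cost is an untested sizing endpoint and room for the analyst to choose the comparison. What power the missing test would have cannot be stated, because the control rate is not given. Over assumed control rates of 47% to 70% it runs from 92% down to 33% two-sided, or 96% down to 45% one-sided.

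**What to change.** Reword the statistical paragraph in 2.13:

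1. Delete the multi-group ANOVA, LSD-t and Tamhane text.
2. State a between-arm comparison of the total effective rate at week 4: GLDS minus placebo with a 95% confidence interval, tested by chi-square, or by Fisher's exact test if expected counts are small. Say which response categories count as effective.
3. Say whether this rate is the primary outcome.
4. Settle sidedness openly and make 2.9 and 2.13 agree. At present 2.9 declares a one-sided test but uses f = 10.5, where the one-sided constant is 8.56.
5. Analyse each scale score by one between-arm contrast at week 4, from ANCOVA with the baseline score as covariate. The baseline scores are already collected. This goes beyond correcting the error, but it makes clear that within-arm changes are descriptive only.

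The cost is rewording one paragraph, with a matching correction in 2.9, before unblinding. No new data, visits or patients are needed for the rewording.

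### No outcome is named primary among four efficacy instruments that share one unadjusted P < .05 threshold, and the total effective rate used for sizing is neither expressly linked to one of them nor given a test

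*Protocol article*

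**What the plan says.** Three sections of the protocol article bear on this.

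- **2.11 Outcomes.** Under the lead-in "The data collected will be the following" come four efficacy items: the Clinical Symptom Rating Scale, the Phlegm-Blood Stasis Syndrome Scale, the Seattle Angina Questionnaire, and the TCM syndrome efficacy criteria. Item 4 is followed by an efficacy index and four grades (significant effect, effective, invalid, aggravation). None of the four items is called primary or secondary, and the section says that before-after changes in the indices will be used to judge whether GLDS works.
- **2.9 Sample size estimation.** The size rests on one quantity: "the total effective rate of GLDS is 86.2% in combination with previous clinical study information". Alpha is 0.05 and beta 0.10, and the result is given as "using a unilateral test, the initial estimated sample number was 27.5, and the integer number was 28".
- **2.13 Data management and statistical analysis.** This section uses another term, "therapeutic effect of angina pectoris are to be observed before and after treatment". It names analysis of variance with pairwise tests, and a rank sum test for non-normal data. Its only decision threshold is P "< .05 will be considered statistically significant". It gives no order among outcomes, no sidedness and no test for a proportion.

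**The concern.** The sample-size section attaches a 5% error rate to one comparison, while the analysis section gives the same 5% to every comparison. Nothing in the text shown says which result carries the effectiveness conclusion. A favourable P value on any one of the instruments could therefore be reported as evidence that GLDS works, and the error rate of that claim would not be the one used for sizing.

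The three sections also use different terms. Section 2.9 speaks of a total effective rate. Section 2.11 gives four grades without saying which of them make up that rate. Section 2.13 speaks of a therapeutic effect on angina and offers only tests for continuous or ranked data. An analyst following 2.13 literally would have no test for the endpoint on which the trial was sized.

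**Working it through.** **1. The plan's own figure.** Inputs from 2.9 are a GLDS rate of 0.862, alpha 0.05, beta 0.10 and f = 10.5. No control rate is given, so 27.5 cannot be reproduced directly. With the usual formula

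n = f × [p1(1 − p1) + p2(1 − p2)] / (p1 − p2)²,

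27.5 per group requires p2 of about 0.4868:

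10.5 × (0.1190 + 0.2498) / 0.3752² = 27.5.

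Rounding up to 28 and allowing for 5% dropout gives 28 / 0.95 = 29.5, hence the stated 30. The calculation is thus compatible with a comparison of two proportions at a single alpha.

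Sidedness is unclear even here. The two-sided constant is (1.9600 + 1.2816)² = 10.51 and the one-sided constant is (1.6449 + 1.2816)² = 8.56. The section says unilateral but uses 10.5, and 2.13 does not state sidedness. Both cases are therefore shown below.

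**2. Error rate if any one test may support the claim, tests independent.**

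- Four tests at 0.05: 1 − 0.95⁴ = 18.5%.
- Three tests at 0.05 (if item 4, for which 2.13 has no test, is not tested): 1 − 0.95³ = 14.3%.
- Four two-sided tests, counting only false benefit (0.025 each): 1 − 0.975⁴ = 9.6%, against 2.5% for one test.

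**3. The same with correlation.** The article gives no correlations, so a common value ρ is assumed and varied. Test statistics were simulated as Xj = √ρ·U + √(1 − ρ)·Ej with standard normal U and Ej, 2 million draws per value of ρ. The ρ = 0 row gives the exact values.

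| ρ (assumed) | 4 tests, two-sided, either direction | 4 tests, one-sided 0.05 | 4 tests, two-sided, false benefit only | 3 tests, two-sided, either direction |
|---|---|---|---|---|
| 0 | 18.5% | 18.5% | 9.6% | 14.3% |
| 0.3 | 17.4% | 16.4% | 8.8% | 13.6% |
| 0.5 | 15.5% | 14.4% | 7.8% | 12.5% |
| 0.7 | 13.1% | 12.0% | 6.5% | 10.9% |
| 0.8 | 11.4% | 10.6% | 5.7% | 9.8% |
| 0.9 | 9.4% | 8.8% | 4.7% | 8.4% |
| single test | 5% | 5% | 2.5% | 5% |

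Every multi-test entry exceeds the single-test value in its column.

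**4. Where the total effective rate comes from.** The grades under item 4 of 2.11 are the only place in the article from which an effective rate could be built, presumably as significant effect plus effective. That link has to be inferred: 2.11 does not use the term, and 2.9 does not name the instrument. The grade boundaries also leave a fall of exactly 30% unassigned, since one grade requires more than 30% and the next less than 30%.

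**The case against.** Several objections have weight.

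- **The sizing endpoint can be traced.** A reader might infer that the total effective rate belongs to none of the four instruments. The article does not support that, because item 4's grades supply it. What remains is that the link is implicit and the rate is not named primary. This stands.
- **The size is conditional.** A reader might take 13–19% as the trial's actual error rate. That range needs correlations of about 0 to 0.7, and it needs either one-sided 0.05 tests or a count of errors in both directions. Items 2 and 4 both appear to rest on the TCM syndrome score, so higher correlation is plausible for that pair. This stands.
- **No decision rule is written down.** Section 2.13 gives a significance threshold. It does not say that one significant scale proves effectiveness, and testing of all four items is itself an inference. This stands, and it is why the figures begin with an if. But nothing in the text shown rules that use out.
- **More tests could be counted.** One might split the Seattle Angina Questionnaire into domains and reach higher rates. The article states no domain count and no domain-level testing, so this is not relied on.
- **A primary outcome may be named elsewhere.** The abstract text, the full protocol and the registry record are not at hand, and multiplicity adjustment is commonly left to an SAP. The finding is therefore limited to the text shown. Even so, the primary outcome belongs in the protocol, because alpha and sample size refer to it, and the article's full sections on outcomes, sizing and analysis do not agree on it.
- **The trial is described as preliminary.** The Discussion calls it so and foresees a larger multicentre study. This softens the consequence, but 2.9 still states a formal alpha and power.

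**Conclusion.** The point holds in a limited form. In the text shown, four efficacy instruments stand as equals, one unadjusted 5% threshold covers them all, and the endpoint that the sample size rests on is neither named primary, nor expressly tied to item 4, nor given a test.

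If any one instrument may support the effectiveness claim, the chance of a false positive is above the stated 5%: 18.5% for four independent tests, about 12–13% at a correlation of 0.7 and about 9–11% at 0.8–0.9. With three tested scales it is 14.3% if they are independent. Counting only false benefit from two-sided tests, it is about 5–10% against 2.5%. These figures assume equal correlation between instruments, normally distributed test statistics and no true effect on any instrument. They are ranges, and no single value can be fixed from the article. The correction should be made, and it is cheap.

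**What to change.** - **2.11:** name one primary outcome, the week-4 total effective rate, defined as the significant-effect and effective grades combined. Keep the symptom-and-sign component of those grades, and assign a fall of exactly 30% to one grade. Label the other three scales secondary, to be reported with 95% confidence intervals.
- **2.13:** name a between-arm comparison of proportions for the primary outcome, for example a chi-square or Fisher exact test, with the risk difference and its 95% confidence interval. State the sidedness and make it agree with 2.9, where the unilateral wording and the constant 10.5 must first be reconciled. State that the effectiveness conclusion rests on the primary outcome alone.
- **2.9, 2.11 and 2.13:** use the same term for this endpoint.

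The choice of primary is the sponsor's. The total effective rate is proposed because 2.9 already sizes on it.

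**Cost:** no extra patients, visits or data; an outcome definition and one added test. The downside is that a lone significant secondary scale can no longer support the claim.
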